## Methods

### Study timeline

Year 1 will focus on planning and collaborative work with two schools, in Seattle, WA and Miami, FL, to pilot school-specific implementation plans. In years 2 through 4, we will conduct a randomized controlled trial comparing (1) STRIPES to (2) SSU + . In each of the three annual cohorts, 24 9th grade students will be recruited at each of the two schools (12 per condition; total *N* = 144) and will be randomized within school and cohort using permuted block randomization. Teachers who nominate students will obtain written parental permission to nominate, a demographic form, and a DSM-5 ADHD checklist [32]. A core academic teacher completes the same ADHD checklist and impairment measures (IRS; [69, 70]). Ninth grade students will be eligible to participate if they display at least 4 symptoms of inattention or hyperactivity/ impulsivity and elevated academic impairment, defined as meeting two of the following: (1) D or F in an academic class, (2) at least 20% of assignments missing in a class, (3) “3” or higher on the teacher IRS academic impairment item (0-6 scale; [70]), (4) elevated score on the teacher Adolescent Academic Problems Checklist (AAPC; 4 items endorsed “pretty much/very much;” [69]). Students are excluded if placed in special education classes, as this study aims to test a low-cost intervention in general education settings. Students with comorbid learning disabilities will be eligible if placed in general education classes. Peer interventionists will be nominated by teachers and must have at least a 3.0 GPA and no suspensions during the past 12 months. Written parental consent and youth assent will be required [70].

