### Assessment procedures

Ecological school outcomes will be collected at five longitudinal time points (once per quarter in 9^th^ grade and once in 10^th^ grade). Target mechanisms will be assessed off medication at the five longitudinal time points and at BL, post-treatment at the end of 9th grade (FU1), and at the beginning of 10th grade (FU2). Compensatory strategies and cognitive processing measures will be collected at BL, FU1, and FU2.

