#### Potential covariates

Medication use will be monitored using the Services for Children and Adolescents-Parent Interview [92]. We will also measure the following potential covariates at BL: intelligence quotient, parent education level, race/ethnicity, age, gender, parent marital status, and free/reduced lunch.

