### Data analysis plan

Analyses will be performed using Mplus version 7 or higher. Missing data will be handled with full information maximum likelihood estimation.

#### Aim 2

The direct effect of STRIPES on each variable (GPA, class attendance, AM, EF) will be evaluated using mixed models [93]. Each outcome will be analyzed with a separate model with time modeled as person-specific (months since BL). We will explore linear, non-linear (i.e., logarithmic, exponential, quadratic), and piece-wise growth models to determine whether there are unique influences of STRIPES on time frames, reflected by slope over time; the best model will be selected using likelihood ratio tests. Effects of time, group, and their interaction will serve as model predictors, and covariates will be included.

#### Aim 3

Aim 3 tests three sets of mediational effects. The mechanisms by which STRIPES affects improvement in student outcome will be evaluated using a structural equation modeling framework in Mplus [94]. Significance of indirect effects will be assessed by bootstrap confidence intervals [95, 96]. In each model, variables that are repeatedly measured (i.e., outcomes, AM, observed EF, rewards processing, motivational strategy, and cognitive control) will be modeled with a mixed model as described in Aim 2. Aim 3a examines the effect of STRIPES on outcomes via AM and observed EF. Aim 3b examines the effect of STRIPES on AM via rewards processing and/or motivational strategy use. Aim 3c examines the effect of STRIPES on observed EF via cognitive control and/or motivational strategy use. For each model, STRIPES predicts the intercept and slope of the mediator model (a paths) and the intercept and slope of the outcome model (c’ paths), while the intercept and slope of the mediator model predict the intercept and slope of the outcome model (b paths).

Current recommendations advise evaluating mediators individually before combining them into a model with simultaneous mediators [97]. For example, Aim 3a will examine AM as a mediator of the STRIPES to outcome relationship in one model, EF as a mediator of the STRIPES to outcome relationship in a second model, and examine both variables as simultaneous mediators in a final model.

#### Aim 4

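### For AM and EF, the Aim 2 model estimates a baseline arm difference that randomisation already sets to zero in expectation, which costs precision but not validity

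*Protocol article*

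**What the plan says.** Under Data analysis plan, Aim 2, the article fits one mixed model per variable (GPA, class attendance, AM, EF). On the time scale it says: "Each outcome will be analyzed with a separate model with time modeled as person-specific (months since BL". On the fixed effects it says: "Effects of time, group, and their interaction will serve as model predictors, and covariates will be included". The effect of interest is described as "unique influences of STRIPES on time frames, reflected by slope over time", that is, the group-by-time term or terms.

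The Aim 3 text confirms that the arm difference at the intercept is left free. Repeated measures there are modelled as in Aim 2, and "STRIPES predicts the intercept and slope of the mediator model (a paths) and the intercept and slope of the outcome model".

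Under Assessment procedures, "Target mechanisms will be assessed off medication at the five longitudinal time points and at BL", and again at FU1 and FU2. For GPA and absences the same section says only that "Ecological school outcomes will be collected at five longitudinal time points", with no separate BL reading. Under Study timeline, students "will be randomized within school and cohort using permuted block randomization". The baseline covariates named under Potential covariates are "intelligence quotient, parent education level, race/ethnicity, age, gender, parent marital status, and free/reduced lunch"; medication use is also monitored. The outcome's own BL value is not listed.

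**The concern.** Because time zero is BL, the group main effect is the arm difference at BL. Students are randomised individually, so its true value is zero if BL is taken before allocation takes effect. The model nevertheless spends a parameter on it and measures the STRIPES slope effect from each arm's own fitted starting point. This is the growth-model counterpart of comparing change scores rather than baseline-adjusted values: sampling noise in the BL means passes into the treatment contrast.

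At stake is the precision of the direct-effect estimates for AM and EF. A model with a common BL mean uses the same data and gives a smaller standard error. GPA and attendance are outside this point because they have no separate BL reading.

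**Working it through.** **The plan's own figure.** The Statistical power section reports power above 0.80 at about 100 participants for medium or larger effects, taken from a cited simulation study. That study's model inputs are not given, so the figure cannot be reproduced from the article.

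**Inputs from the article.** N = 144, 1:1 allocation, 5% attrition: 144 × 0.95 / 2 = 68.4 per arm. The paths from STRIPES to the mediators in Aims 3a and 3b are expected to be d = 0.85 to 2.05; the Aim 3a mediators are AM and observed EF. The path size above which Aim 3 is said to have sufficient power is d = 0.35.

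**Assumptions.** Two-sided 5% test and SD 1. Occasions at 0, 2, 4.5, 7, 9 and 12 months (six), or 0, 9 and 12 months (three: BL, FU1, FU2). Correlation ρ of 0.3, 0.5 or 0.7. Two covariance structures: compound symmetry, and autoregressive decay with measurement error, 0.85 × ρ^(lag/9) plus 0.15 on the diagonal. In the second, the nine-month correlation is 0.85ρ.

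**Two-occasion case.** With a free BL difference the contrast has variance proportional to 2(1 − ρ). With a common BL mean it is 1 − ρ². The ratio is (1 + ρ)/2, which is 0.65, 0.75 and 0.85 at ρ = 0.3, 0.5 and 0.7. Square roots are 0.81, 0.87 and 0.92, so the standard error falls by about 19, 13 and 8%.

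**Growth model, linear time.** The generalised-least-squares information is the sum over students of X'V⁻¹X. X holds intercept, time and group-by-time, with or without the group main effect. The contrast is 12 × the group-by-time slope. Each cell gives the standard error with a free BL difference, then with a common BL mean, then the reduction.

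| Structure | ρ = 0.3 | ρ = 0.5 | ρ = 0.7 |
|---|---|---|---|
| Six occasions, compound symmetry | 0.172 / 0.138 (19.8%) | 0.145 / 0.128 (11.7%) | 0.112 / 0.106 (6.0%) |
| Six occasions, autoregressive | 0.217 / 0.162 (25.1%) | 0.193 / 0.157 (18.6%) | 0.161 / 0.141 (12.2%) |
| Three occasions, compound symmetry | 0.194 / 0.144 (26.0%) | 0.164 / 0.135 (17.6%) | 0.127 / 0.114 (10.0%) |
| Three occasions, autoregressive | 0.219 / 0.163 (25.5%) | 0.196 / 0.158 (19.4%) | 0.165 / 0.143 (13.5%) |

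**Other time shapes.** With log(1 + months), or piecewise time with a knot at 4.5 or 9 months, the gain persists. Across all these runs, linear included, the reduction ran from 3.7% (six occasions, compound symmetry, ρ = 0.7, knot at 9 months) to 29.1% (six occasions, compound symmetry, ρ = 0.3, logarithmic).

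**Random slopes.** With random intercept and slope (variance 0.9 at BL rising to 1.2) and ρ = 0.5, the figures are 0.160 / 0.150 for six occasions and 0.174 / 0.156 for three: reductions of 6% and 10%. In the least favourable case tried (six occasions, ρ = 0.7, slope variance 0.2, intercept–slope correlation 0.3), the variance ratio was 0.98, so the standard error fell by only about 1%.

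**Power**, as Φ(d/SE − 1.96) from unrounded standard errors:

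- d = 0.85, largest free-baseline standard error in the table (0.219): 0.85/0.219 − 1.96 = 1.92, power 0.97. Elsewhere in the table it is higher.
- d = 0.35, six occasions, ρ = 0.5, compound symmetry: 0.67 free, 0.78 common.
- d = 0.35, six occasions, ρ = 0.5, autoregressive: 0.44 free, 0.60 common.

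**The case against.** Time, group and their interaction make a standard growth model that is valid under randomisation, and many analysts would leave the intercept free. That stands: this is a matter of efficiency. A reader might infer bias, since a chance BL imbalance feeds into the slope contrast through regression to the mean. Over repeated randomisations such imbalance averages out; it adds noise, which the standard errors above already count.

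A reader might also infer that power drops below the plan's 0.80, because the smallest effect listed for Aim 2 is d = 0.47. At ρ = 0.5 with six occasions and linear time, the free-baseline model would give 0.90 (compound symmetry) or 0.68 (autoregressive) at that effect. The article does not support applying 0.47 here. It does not say which outcome that value belongs to, and it puts the effects on AM and observed EF within 0.85 to 2.05. At 0.85, power is already about 0.97 or more.

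It can further be said that constraining the intercept is a detail for the full analysis plan. But the article does state the predictors, and Aim 3 makes the free intercept explicit, so this is a stated choice rather than a gap. Finally, the size rests on a correlation, covariance structure and visit months that the article does not give. That is correct, and the result is a range that reaches close to nothing in the least favourable random-slope case.

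**Conclusion.** The point holds as a loss of precision for AM and EF in Aim 2. With 68.4 per arm and ρ from 0.3 to 0.7, a common BL mean lowers the standard error of the end-of-follow-up STRIPES effect by roughly 5 to 30% under compound-symmetry or autoregressive structures, whether time is linear, logarithmic or piecewise. With random slopes the gain can be smaller. At the effects expected for AM and observed EF, conclusions from the test would hardly change, and the gain is in narrower intervals. It becomes a gain in power if true effects are smaller. That is possible, since the expected values come from one earlier trial of 72 students.

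The argument needs BL to be measured before allocation takes effect. The Comparison section points that way, because SSU+ students are referred to the counselor with their BL assessment, but the article does not state the order outright.

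**What to change.** For AM and EF in Aim 2, keep BL in the outcome vector, fix the group effect on the intercept at BL to zero, and test STRIPES by the group-by-time term or terms. In Mplus this fixes the regression of the intercept factor on group at zero. Report the free-intercept fit as a sensitivity analysis, and state that BL precedes allocation.

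If BL is instead entered as a covariate and only post-BL occasions are modelled, STRIPES must be tested by the group effect at those occasions (group plus group-by-time). Group-by-time alone would then miss an effect already present at the first post-BL occasion; for measures taken only at BL, FU1 and FU2 it would test only the FU1-to-FU2 change.

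For consistency, put the same zero constraint on the STRIPES-to-intercept paths in Aim 3 for variables with a pre-randomisation BL reading.

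The cost is a short addition to the Aim 2 and Aim 3 text and one fixed parameter per affected growth model, with no new data. The small downside is reliance on the common-baseline assumption.

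### In Aim 3 the STRIPES-to-intercept paths point at baseline levels, so they cannot be treatment effects; read literally, one b path also runs backward in time

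*Protocol article*

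**What the plan says.** All of this is in the protocol article, Methods.

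- **Time origin.** Under Data analysis plan, Aim 2, each outcome has its own mixed model with "time modeled as person-specific (months since BL").
- **Carried into Aim 3.** Repeatedly measured variables in the mediation models "will be modeled with a mixed model as described in Aim 2".
- **a and c' paths.** In each Aim 3 model, "STRIPES predicts the intercept and slope of the mediator model (a paths) and the intercept and slope of the outcome model"; the first pair are labelled a paths and the second pair c' paths.
- **b paths.** "the intercept and slope of the mediator model predict the intercept and slope of the outcome model (b paths").
- **Inference.** "Significance of indirect effects will be assessed by bootstrap confidence intervals". No single indirect effect is named as the one to be interpreted.
- **Allocation.** Under Study timeline, students are "randomized within school and cohort using permuted block randomization".
- **Measurement.** Under Assessment procedures, "Compensatory strategies and cognitive processing measures will be collected at BL, FU1, and FU2". Academic motivation (AM) and executive functioning (EF) are assessed at those three occasions and at five longitudinal points. GPA and absences are listed once per quarter in 9th grade and once in 10th grade, with no separate baseline occasion.

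The model diagrams are in Fig. 2, which is not available here.

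**The concern.** A growth-model intercept is the expected level when time is zero. With time counted from baseline, that is the pre-treatment level. Randomisation makes the expected arm difference there zero, yet the plan classes the paths from STRIPES to these intercepts with the treatment effects on the mediator and the outcome.

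The b-path sentence adds a second difficulty if it means every crossing of mediator intercept and slope with outcome intercept and slope. The mediator slope is formed after baseline and would then explain the outcome level at baseline.

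Aim 3 is the mechanism test. It bears on the question under Study aims of whether STRIPES repairs underlying cognitive deficits, builds compensating skills, or both. With several indirect products per model and none singled out, a bootstrap interval for a product that cannot be a treatment effect could be reported as mediation.

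**Working it through.** **Plan figure.** 24 students × 2 schools × 3 cohorts = 144, as stated. The Aim 3 power statement (a and b paths above d = 0.35) is not in dispute here.

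**Step 1: list the indirect products for one mediator, with time 0 at baseline.**

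| Path from STRIPES | All-crossings reading | Parallel reading | Can it be a treatment effect? |
|---|---|---|---|
| mediator intercept → outcome intercept | present | present | no: both at baseline |
| mediator intercept → outcome slope | present | absent | no: starts from baseline imbalance |
| mediator slope → outcome intercept | present | absent | no: backward in time |
| mediator slope → outcome slope | present | present | yes |

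The non-causal share is 3 of 4 on the all-crossings reading and 1 of 2 on the parallel reading. STRIPES-to-intercept paths are in the model on both.

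**Step 2: what the backward path yields.** Let the baseline outcome be unrelated to arm but have residual correlation ρ with the mediator slope (unit-variance factors). Regressing the baseline outcome on arm and mediator slope gives b ≈ ρ. The product is then a·ρ and the direct path is −a·ρ, which sum to zero.

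- a = 0.85, ρ = 0.15: 0.85 × 0.15 = 0.13
- a = 0.85, ρ = 0.30: 0.85 × 0.30 = 0.26
- a = 0.35, ρ = 0.30: 0.35 × 0.30 = 0.11

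The value 0.85 is the lower end of the a-path range under Statistical power, and 0.35 is the threshold given there. The values of ρ are assumptions.

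Simulation: N = 144, 1,500 replicates per setting, growth factors treated as observed, slope-to-slope b of 0.3, ρ also applied between mediator intercept and baseline outcome, and Monte Carlo intervals for the product in place of the bootstrap. Share of trials in which the 95% interval for STRIPES → mediator slope → outcome intercept excludes zero:

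| a | ρ = 0 | ρ = ±0.15 | ρ = ±0.3 |
|---|---|---|---|
| 0.35 | 2% | 23–24% | 54–55% |
| 0.85 | 6% | 43–46% | 97% |

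At a = 0.85 the mean product was 0.124 (ρ = 0.15) and 0.256 (ρ = 0.3), offset by direct paths of −0.122 and −0.251, in line with the algebra. The two products through the mediator intercept averaged about zero, and their intervals excluded zero in at most 6.4% of trials in any setting.

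**Step 3: precision gained by the baseline constraint.** With equal arms, time t in years and V = ρ_w·J + (1 − ρ_w)·I + s²·tt′ (J all ones, I the identity), the variance of the STRIPES slope effect with the baseline difference fixed at zero, divided by that with it free, is

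ratio = 1 − (1′V⁻¹t)² / [(1′V⁻¹1)(t′V⁻¹t)].

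Example: months 0, 8, 12, ρ_w = 0.3, s² = 0. Then 1′V⁻¹1 = 3/1.6 = 1.875; 1′V⁻¹t = (5/3)/1.6 = 1.042; t′V⁻¹t = (13/9 − 0.1875 × 25/9)/0.7 = 1.319. Ratio = 1 − 1.085/2.474 = 0.56.

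| Assumed waves (months) | ρ_w 0.3–0.7, s² 0–0.3 | ρ_w 0.5, s² 0.1–0.3 |
|---|---|---|
| 0, 8, 12 | 0.56–0.88 | 0.72–0.77 |
| 0, 2.5, 5, 7.5, 12 | 0.65–0.93 | 0.80–0.84 |

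Wave times, correlations and slope variances are all assumed. The five-wave layout only approximates the stated schedule.

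**The case against.** The best reply is that the b-path sentence is ambiguous. It may mean intercept to intercept and slope to slope, and Fig. 2, which would settle this, is not shown. This stands. A reader might infer that most of the Aim 3 indirect effects are non-causal, but that holds only on the all-crossings reading. The sentence has no word pairing the terms, so that reading is the literal one, but it is not certain.

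A second reply is that free STRIPES-to-intercept paths do little harm, since they are zero in expectation and do not bias the slope effects. This also stands. The harm is mislabelling, extra tests and lost precision. The variance ratios measure only that precision and say nothing about causal validity. Their lowest value needs a correlation of 0.3 with no slope variance, which is an unlikely corner.

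Three further inferences are not supported:

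- That the Aim 2 group main effect loses precision as a slope effect. In that model it is the difference at time zero.
- That in Aims 3b and 3c the mediators are re-measured only after the AM and EF values they should drive. AM and EF are also measured at FU1 and FU2.
- That concurrent slope-to-slope mediation is an error in this plan. Overlapping change is a general limit of such models, and the plan also allows piecewise growth. It calls for a stated caveat.

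Finally, GPA and absences have no separate baseline occasion listed. Their month-0 intercept is an extrapolation, so a zero constraint should not be imposed on them as a matter of course.

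**Conclusion.** The concern holds in limited form. Given the stated time origin and randomisation, the STRIPES-to-intercept paths cannot be treatment effects, whichever way the b-path sentence is read. This is firmest where a baseline measurement exists: AM, EF, and the cognitive and strategy measures. It assumes that BL precedes randomisation. The Comparison section fits this, since control students are referred with their baseline assessment. It also assumes that time is not re-centred at a later point; no re-centring is stated.

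The backward path is conditional on the all-crossings reading. If it is in the model, it can produce a clearly significant indirect effect with no treatment effect on the baseline outcome, provided mediator slope and baseline outcome are correlated; at zero correlation the rate is about 2–6%.

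The precision gain is secondary: a variance multiplier of about 0.56–0.93 over the assumed range, and 0.72–0.84 at correlation 0.5 with slope variance 0.1–0.3. The Aim 2 effectiveness conclusion does not depend on this point.

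**What to change.** 1. For measures with a pre-randomisation BL (AM, EF, cognitive and strategy measures), set the STRIPES-to-intercept path to zero and let the mediator and outcome intercepts covary.
2. Omit any path from mediator slope to outcome intercept, and carry that association as a covariance. If the b paths were meant in parallel, say so in the text.
3. Name STRIPES → mediator slope → outcome slope as the only indirect effect interpreted as mediation, and state that mediator and outcome change overlap in time, so their order is not established.
4. For GPA and absences, state what the month-0 intercept represents and do not report a STRIPES path to it as a treatment effect on baseline.
5. Optionally add, as a sensitivity analysis, a lagged model from mediator change between BL and FU1 to the later outcome. It should not replace the main model: for GPA and attendance it would discard the 9th-grade quarters.

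The cost is a change in model specification, with no new data or visits. The optional lagged analysis costs only the additional model.

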### Ninth grade as a strategic window for intervention

Ninth grade is an important time for students with ADHD to access services. Performance during this year is a robust predictor of HS dropout [41]. Further, declines in grade point average (GPA) [42], self-esteem [43], and adjustment to HS are prevalent among adolescents at this age, and this is prominent in students with ADHD, whose 9th grade year is the trough of their academic performance [4]. Interventions for ADHD may be particularly effective when delivered in 9th grade. In previous work [27], our team delivered a summer program to rising 6th and 9th graders with ADHD. The intervention had greater effects on symptoms and functioning in 9th (vs. 6th) graders. We hypothesize that greater cognitive maturity in 9th graders promoted skill uptake and generalization.

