#### Statistical power

We estimate 5% attrition based on previous studies. Statistical models are outlined in Fig. 2. Aim 2. Based on simulations by Fan [101], we assessed statistical power for mixed models, given a fixed sample size of 144. Based on previous research [44], we expect group differences at later time points to range from medium to very large (*d* = 0.47, 0.85, 1.11, 1.47, 1.69, 2.05 for primary outcomes); Fan [101] found that statistical power exceeded 0.80 with samples of about 100 with medium or larger effects. Aim 3. For the indirect effects proposed in Aims 3a-3c, statistical power estimates are based on sample size calculations by Fritz and MacKinnon [102]. Statistical power for the indirect effect depends entirely on the values of the “a path” (X to M effect) and “b path” (M to Y effect) effect sizes. With a sample size of 144 and using preferred bootstrap methods, we have sufficient power to detect the indirect effect provided both the “a path” and the “b path” are greater than *d* = 0.35. Prior research [44] shows “a paths” for Aims 3a and 3b that range from *d* = 0.85 to 2.05. Aim 4. We will assess statistical power of the cost-effectiveness analysis using methods outlined by Boyd and colleagues [103]. Aim 5. Due to the complexity of estimating statistical power for the mixed models in Aim 5, we base our estimates of power on effects from the previous STRIPES trial [44], which used similar models for analysis with a substantially smaller sample. We used F statistics to estimate the non-centrality parameter, estimated a denominator degrees of freedom based on more observations (144 students each measured 5 times versus 72 students each measured 4 times), and estimated statistical power for a generic F test based on these values. Of the 35 effects examined, the mean power value was 0.61. Seven effects had estimated power > 0.80; based on the non-centrality parameters for these effects, we have adequate power to detect effects as small as Cohen’s *d* = 0.245, which is a small effect size.

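### Aim 3 does not adjust the mediator-slope to outcome-slope path for the student's starting outcome, so a starting level that drives both slopes can produce a false indirect effect

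*Protocol article*

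**What the plan says.** The Aim 3 part of the Data analysis plan in the protocol article describes two linked growth models, one for the mediator and one for the outcome. It lists three sets of paths for each model:

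- a paths: STRIPES to the mediator intercept and slope.
- c' paths: STRIPES to the outcome intercept and slope.
- b paths: "the intercept and slope of the mediator model predict the intercept and slope of the outcome model (b paths".

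The outcome intercept therefore appears only as a dependent variable. The growth models follow Aim 2, where time is months since baseline and covariates are included but not named. The Potential covariates section lists medication use, IQ and demographic items. It names no baseline GPA, attendance, motivation or executive-function score. Baseline GPA is named only as an Aim 5 moderator.

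The indirect effect is tested by bootstrap intervals. The Statistical power section expects a paths of d = 0.85 to 2.05 for Aims 3a and 3b.

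**The concern.** Students are "randomized within school and cohort using permuted block randomization". This protects the effect of STRIPES on the mediator and the total effect on the outcome. It does not protect the path from mediator to outcome, because students are not allocated to a mediator slope.

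A student's starting level on the outcome precedes treatment and may be related to later change in both processes. For example, a student with very low grades may have more room to improve in both organisation and grades. If so, the two slopes move together even when the mediator has no effect on the outcome. The mediator's own intercept is in the model, but it only partly stands in for the outcome's starting level. A residual covariance between outcome intercept and outcome slope, if estimated, would not adjust b either.

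With a paths as large as the plan expects, the a part of the product is almost certain to be significant, so the test of the indirect effect is in practice a test of b. At stake is the claim about how STRIPES works. The Aim 2 effectiveness result is not affected.

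**Working it through.** **Inputs from the protocol article.** The plan states that "24 9th grade students will be recruited at each of the two schools", over three annual cohorts: 24 x 2 x 3 = 144, which matches "given a fixed sample size of 144" and gives 72 per arm. The a path is taken at the low end of the stated range, d = 0.85. The plan gives no figure for confounding of b.

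**Assumed.** True mediation zero; two-sided alpha 0.05; linear growth; complete data; correlations g (starting outcome with mediator slope) and k (starting outcome with outcome slope). The documents give neither g nor k, so a range is shown.

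**Step 1: the a path.** z = 0.85 x sqrt(72/2) = 5.1, so it is significant almost always. With slope reliability 0.5, d shrinks to 0.85 x sqrt(0.5) = 0.60 and z = 3.6, giving power of about 95%.

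**Step 2: the spurious b.** If the starting outcome is the only link between the slopes, they correlate within arm at r = g x k. With both slopes at reliability 0.5 the observable correlation is 0.5 x g x k. The outcome-slope equation has four coefficients (constant, STRIPES, mediator intercept, mediator slope), so z = r x sqrt(144 - 4) / sqrt(1 - r²), with sqrt(140) = 11.83. The false-positive rate is P(|Z + z| > 1.96). This treats the mediator intercept as unrelated to the starting outcome and the a path as certain, so it runs slightly high.

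| g, k | r, error-free | z | rate | r, reliability 0.5 | z | rate |
|---|---|---|---|---|---|---|
| -0.2, -0.3 | 0.06 | 0.71 | 11% | 0.03 | 0.36 | 6% |
| -0.3, -0.4 | 0.12 | 1.43 | 30% | 0.06 | 0.71 | 11% |
| -0.4, -0.5 | 0.20 | 2.42 | 68% | 0.10 | 1.19 | 22% |

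**Step 3: simulation of the indirect-effect test.** Two separate runs agree closely; ranges span both.

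| g, k | as written, reliability 0.5 | as written, error-free | outcome intercept added |
|---|---|---|---|
| 0, 0 | 5% | 4% | 4% |
| -0.2, -0.3 | 4 to 5% | 10% | 4 to 5% |
| -0.3, -0.4 | 10 to 11% | 24 to 26% | 5% |
| -0.4, -0.5 | 19 to 22% | 59 to 60% | 6% |

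**Step 4: what drives the bias.** A further simulation generated five waves per student and used percentile bootstraps (300 trials of N = 144, Monte Carlo error about 1.3 points at a 5% rate). True mediation was zero, and a = 0.85 except in the last row. Selected means enrolled for a low starting outcome. The numbers 0.5 and 0.75 are slope change per unit of starting outcome.

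| Scenario | as written | adjusted |
|---|---|---|
| Selected, pure regression to the mean | 7% | 4% |
| Selected, low start drives outcome slope only (0.5) | 7% | 6% |
| Selected, low start drives both slopes (0.5) | 16% | 7% |
| Selected, low start drives both slopes (0.75) | 48% | 5% |
| Not selected, low start drives both slopes (0.5) | 76% | 7% |
| Selected, shared transient states, correlation 0.5 | 92% | 58% |
| Selected, drives both slopes (0.5), a = 0 | 0% | 0% |

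In the shared-states row the large-sample b is 0.53 as written and 0.58 adjusted, against a true value of zero. The lower rejection rate there reflects lost precision, not removed bias.

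**Step 5: can the model carry the extra paths?** Four growth factors and arm supply 10 variances and covariances plus 4 covariances with arm, or 14 moments.

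- Listed paths plus outcome intercept to outcome slope: 4 arm paths + 4 b paths + 1 + 4 disturbances = 13. A mediator intercept-slope covariance makes 14. A residual outcome intercept-slope covariance on top would make 15, so the new path has to replace it.
- Regressing both slopes on both intercepts while keeping the plan's mediator-slope to outcome-intercept path: 4 arm paths + 7 paths among factors + 4 disturbances = 15, which is under-identified (rank 14). Dropping the mediator-slope to outcome-intercept path gives 14 parameters with rank 14, which is identified.

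**The case against.** **The omission is read from a condensed text.** Fig. 2, which outlines the models, is not shown, the covariates are unnamed, and the full plan may contain the path. This stands as a limit on confidence. But the article does set out the predictors of the outcome slope, and neither they nor any named covariate supplies the starting outcome.

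**The size rests on assumed correlations.** This also stands. At the weakest pair with reliability 0.5 there is nothing to correct. The figures near 60% need error-free slopes, which five waves will not give. Without a real a path there is no inflation.

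**A stronger reading is tempting.** Entry depends on "meeting two of the following: (1) D or F in an academic class, (2) at least 20% of assignments missing in a class" or on teacher ratings, and the plan describes students with ADHD as those "whose 9th grade year is the trough of their academic performance". A reader might infer that the recovery of students chosen for failing itself creates false mediation. The check does not support this. Regression to the mean in the outcome alone leaves b near zero. With the starting outcome driving both slopes at 0.5, false mediation was 76% without selection and 16% with it, because selection narrows the spread of starting levels. The necessary condition is that the starting outcome drives the mediator slope as well as the outcome slope.

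**Aims 3b and 3c differ.** Their outcomes are motivation and observed executive function, so the grades example fits Aim 3a best, and the large a paths are stated only for 3a and 3b. The structural gap is the same in all three, but the argument that the test reduces to b is not documented for 3c.

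**Conclusion.** The point holds in conditional form. As described, the b path that carries the mechanism claim is not adjusted for a pre-treatment variable that the trial already measures. If that variable drives both slopes and STRIPES truly moves the mediator, a false indirect effect can follow. The rate is roughly 10 to 20% at slope reliability 0.5 and about 25 to 60% with error-free slopes, at correlations of -0.3 and -0.4 up to -0.4 and -0.5. Under weaker dependence with reliability 0.5 it stays near 5%.

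This rests on the assumed correlations, linear growth, complete data (the plan expects 5% attrition, which would take sqrt(140) only to about sqrt(133)), and an outcome intercept that represents the level at baseline. It does not show that the trial will report false mediation, that selection for failing grades is the cause, or that adjustment makes b causal. The change should be made. Confidence is medium because Fig. 2 and the full plan are not available.

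**What to change.** In each Aim 3 model, add the outcome intercept as a predictor of the outcome slope, in place of a residual covariance between the two. Take b as the coefficient of the mediator slope in that equation, and form the indirect effect from that b and the arm-to-mediator-slope path only.

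If the mediator slope is also regressed on the outcome intercept, drop the path from mediator slope to outcome intercept. With time counted from baseline, later change cannot cause the baseline level, and keeping both directions leaves the model under-identified.

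State with the result that the indirect effect assumes no remaining mediator-outcome confounding, including shared time-varying causes, which this adjustment does not address. If Fig. 2 or the full plan already contains the path, say so in the text.

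The cost is one or two paths per model on data already collected, and a slightly wider interval for b when the starting outcome is unrelated to change. In that case the adjusted test still held its error rate, at about 4%.
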